#### Clinical and laboratory data

Fasting blood samples will be analysed for full blood count, urea, creatinine and electrolytes, thyroid stimulating hormone (TSH), lipid profile (total cholesterol, high-density lipoprotein, triglycerides), liver function tests, prothrombin time, international normalised ratio (INR), amylase, α-fetoprotein, C reactive protein, HbA1c, calcitonin and plasma glucose using standard laboratory methods (Roche Modular system, Roche Ltd, Lewes, UK). Serum Insulin (Mercodia, Uppsala, Sweden), non-esterified fatty acids (Zen-Bio, Research Triangle Park, North Carolina, USA) and CK-18 M30 (M30 Apoptosense ELISA Kit; PEVIVA AB, Bromma, Sweden) will be measured in-house using commercially available colorimetric ELISAs. Serum caspase-cleaved cytokeratin-18 (CK-18 M30) and the ELF Test were performed at study entry to assess hepatic apoptosis and fibrosis, respectively. The FibroMax panel (consisting of the SteatoTest, NashTest, FibroTest) will be undertaken by Lab 21 Ltd (Cambridge, UK). The ELF test, which combines three direct serum markers of fibrosis (hyaluronic acid, pro-collagen III amino terminal peptide and tissue inhibitor of metalloproteinase 1) using an algorithm developed by the European Liver Fibrosis Group,^36^ will be performed on fasting serum stored at −80° by a commercial laboratory (iQUR Ltd, Royal Free Hospital, London, UK).

T2D was considered present if patients had a recorded diagnosis in their medical records or if the fasting plasma glucose was ≥7 mmol/L and/or if the 2 h 75 g oral glucose tolerance test (OGTT) plasma glucose was ≥11.1 mmol/L. All patients without a recorded history of T2D were screened with an OGTT. Impaired glucose tolerance (IGT) was defined as a 2 h plasma glucose between 7.8 and 11.1 mmol/L. HOMA-IR, a marker of insulin resistance, was calculated in the standard fashion: glucose×insulin/22.5.

Measurements of weight (kg), height, systolic/diastolic blood pressure and waist:hip circumferences were recorded. Waist and hip circumferences were defined as the circumferential measurements immediately above the level of the iliac crests and at the level of the greater trochanters, respectively. BMI was defined as weight in kilograms divided by the square of the height in metres (kg/m^2^).

LSE was measured using Transient Elastography (Fibroscan, Echosens, France). The median value and IQR of 10 validated measurements were recorded within the range of 2.5–75 kPa. The XL probe was used on individuals who have a BMI greater than 30 kg/m^2^ or when the Fibroscan 502 Touch machine (automated) recommends its use over the M-probe. To achieve a valid LSE (median of successful liver stiffness measurements) the operator had to obtain all of the following three criteria: (1) ≥10 successful liver stiffness measurements; (2) IQR/median ratio <0.30 and (3) ≥60% measurement success rate.^37^

#### Patient questionnaires

QOL was assessed by the Short Form 36 V.2.0 (SF-36v2) health-related QOL questionnaire (QualityMetric Health Outcomes Solutions, Lincoln, USA). The SF-36v2 questionnaire was a practical, reliable and valid measure of physical and mental health that could be completed in 5–10 min. It consisted of 36 questions that assessed the functional health and well-being from the study participant's point of view.^38^ The Block Brief 2000 FFQ (Block Dietary Data Systems, California, USA) was completed by each participant to assess the usual and customary intake of a wide array of nutrients and food groups. The food list incorporated in the Block questionnaire was developed from the National Health and Nutrition Examination Survey III dietary recall data. The Block Brief 2000 FFQ consisted of a well-validated self-administered questionnaire consisting of 70 food-related questions and took approximately 15 min to complete.^39^ Pictures of standardised serving sizes and an American-to-English food translation sheet (ie, ‘Catsup’=tomato ‘Ketchup’) were used to aid completion of the questionnaire.

The Alcohol Use Disorder Identification Test (AUDIT) questionnaire was used to assess the frequency of alcohol consumption and screen out alcohol-related problems, and dependence symptoms.^40^ The AUDIT questionnaire consisted of a 10-item questionnaire that took 2–5 min to complete. The questionnaire has a positive predictive value of 98% for hazardous drinking, and a negative predictive value of 97% for alcohol dependence. The overall score ranges from 0 to 40, with a score of less than 8 being a good indication of insignificant alcohol consumption.

All questionnaires were completed at baseline (visit 1), end-of-treatment (visit 7) and 12 weeks post-treatment (visit 8). Analysis will report the change from baseline scores to both the end-of-treatment and follow-up scores.

### Statistical justification and outcome analysis

#### Sample size justification

This is an early phase II trial randomising patients equally between two treatment arms—one experimental (liraglutide) and one control (placebo). The primary aim is not to determine the efficacy of liraglutide compared with placebo but to assess whether the efficacy and safety profile of liraglutide is worthy of further investigation. Recruiting patients into a no-treatment control group provides simultaneous unbiased assessment of comparable patient groups.

At the time of the study design there were no available data to estimate histological response with a 48-week treatment of liraglutide (Victoza). Based on previous non-GLP-1 pharmaceutical trials in NASH utilising improvements in liver histology as a primary endpoint,^41^
^42^ it was assumed that 14–17% of patients undergoing current standard of care (placebo) would have an improvement in NASH by week 48. It was estimated that 20% of the placebo-control arm would achieve an improvement in liver histology, based in part on the knowledge that the placebo effect might be exaggerated by the subcutaneous injection route of administration (vs oral route in previous NASH trials) in the current trial. To justify further investigation of liraglutide treatment, a clinically relevant improvement in liver histology was required in at least 50% of patients. The sample size was calculated using A'Hern's single stage phase II methodology,^43^ with a significance level of 0.05 (type 1 error) and power of 0.90 (type II error). The design required 21 evaluable patients in the treatment group. The published literature in NASH trials reported on average a participant withdrawal rate of 10–20%.^41^
^42^
^44^ Therefore, to account for a 20% withdrawal rate the recruitment target was inflated from 21 to 25 patients per treatment group; the total recruitment target being 50 patients randomised in a 1:1 allocation ratio to either liraglutide or placebo.

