**Methods and analysis:**

Liraglutide efficacy and action in NASH (LEAN) is a phase II, multicentre, double-blinded, placebo-controlled, randomised clinical trial designed to investigate whether a 48-week treatment with 1.8 mg liraglutide will result in improvements in liver histology in patients with NASH. Adult, overweight (body mass index ≥25 kg/m^2^) patients with biopsy-confirmed NASH were assessed for eligibility at five recruitment centres in the UK. Patients who satisfied the eligibility criteria were randomly assigned (1:1) to receive once-daily subcutaneous injections of either 1.8 mg liraglutide or liraglutide-placebo (control). Using A'Hern's single stage phase II methodology (significance level 0.05; power 0.90) and accounting for an estimated 20% withdrawal rate, a minimum of 25 patients were randomised to each treatment group. The primary outcome measure will be centrally assessed using an intention-to-treat analysis of the proportion of evaluable patients achieving an improvement in liver histology between liver biopsies at baseline and after 48 weeks of treatment. Histological improvement will be defined as a combination of the disappearance of active NASH and no worsening in fibrosis.

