### Analysis of outcome measures

All evaluable patients will be analysed on the intention-to-treat principle. Evaluable patients are defined as those who have had an end-of-treatment biopsy (visit 7), irrespective of the amount of treatment they have received. Patients will be categorised as either achieving the primary histological endpoint (ie, disappearance in NASH) or not. The proportion of patients with a reported improvement in liver histology will be presented and compared across treatments descriptively with 95% CIs. The proposed A'Hern's design stipulates that 8 or more evaluable patients of 21 in the experimental treatment group (liraglutide) need to achieve the defined improvement in liver histology for treatment with liraglutide to be deemed worthy of further investigation with a phase III trial. Analyses will be presented for the subgroups of patients with and without T2D. Patients who have not had an end-of-treatment biopsy will be classed as non-evaluable and will not be included in the primary analysis.

Secondary analysis of the primary outcome measure will report (1) the number and proportion of patients that did not have an end-of-treatment biopsy and the reasons for this (these will be classified as ‘no histological improvement’) and (2) the number and proportion of patients that were considered to have had sufficient treatment and an end-of-treatment biopsy. In addition, an analysis that directly compares the two proportions for the separate treatment arms will be performed using the χ^2^ test.

Secondary measures collected as continuous and categorical variables will be presented with 95% CIs descriptively across treatments using medians and proportions, respectively. Secondary measures collected as longitudinal data (including QOL data, scored as per the questionnaire-specific scoring manuals) will be presented descriptively across treatment groups as changes over time. A summary of all adverse events (AEs) experienced by patients in both arms will be reported.

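### Randomising 25 per arm does not allow for 20% withdrawal: it leaves 20 evaluable patients, not the 21 the design needs, and power is about 0.87 rather than 0.90

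*Protocol article*

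**What the plan says.** The section Sample size justification gives every input. The method is a single-stage design: "The sample size was calculated using A'Hern's single stage phase II methodology", "with a significance level of 0.05 (type 1 error) and power of 0.90 (type II error"). For the response rate that would not be of interest, "It was estimated that 20% of the placebo-control arm would achieve an improvement in liver histology". For the target rate, "a clinically relevant improvement in liver histology was required in at least 50% of patients". The result is that "The design required 21 evaluable patients in the treatment group".

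The section cites withdrawal of 10–20% in earlier trials, adopts the upper figure and says that "to account for a 20% withdrawal rate the recruitment target was inflated from 21 to 25 patients per treatment group", which makes 50 in total. The abstract repeats the claim next to the stated power of 0.90: "accounting for an estimated 20% withdrawal rate, a minimum of 25 patients were randomised to each treatment group".

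The section Analysis of outcome measures sets the decision rule: "8 or more evaluable patients of 21 in the experimental treatment group (liraglutide) need to achieve the defined improvement in liver histology". It also leaves patients without an end-of-treatment biopsy out of the primary analysis. They are counted as non-improvers only in a secondary analysis.

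**The concern.** A withdrawal rate is a share of the patients randomised. The number to randomise is therefore the evaluable number divided by the share retained. The stated target of 25 is too small for that. It matches 21 increased by 20% and rounded down, which applies the rate to the evaluable patients instead.

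Because patients without the final biopsy drop out of the primary analysis, each such loss reduces the denominator of the single-arm test directly. In a design this small, one patient moves power by almost four percentage points. At stake is the stated chance of detecting a treatment worth taking to phase III. Someone interpreting a negative result would believe that the risk of a false negative was at most 10% under the planned withdrawal, when it is higher.

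**Working it through.** **Inputs** (protocol article, Sample size justification and Analysis of outcome measures): p0 = 0.20, p1 = 0.50, type I error at most 0.05, power at least 0.90, 21 evaluable patients, cut-off 8, withdrawal 20%, target 25 per arm. The article does not state sidedness; the A'Hern test is one-sided. The number randomised, 52, is from Trial status.

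**Formulas.** For n evaluable patients and cut-off r:
- type I error = P(X ≥ r), with X ~ Binomial(n, 0.20)
- power = P(X ≥ r), with X ~ Binomial(n, 0.50)
- number to randomise = evaluable number / (1 − withdrawal rate), rounded up

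**Step 1: the base design reproduces.** For n = 21 and r = 8, type I error is 0.0431 and power is 0.9054. No smaller n meets both limits. The inputs are therefore read as intended, and 21 with cut-off 8 is correct.

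**Step 2: the inflation does not reproduce.**
- Correct step: 21 / (1 − 0.20) = 26.25, so 27 per arm and 54 in total. Expected evaluable: 27 × 0.80 = 21.6.
- Stated target: 25 × 0.80 = 20.0, one short of 21.
- Apparent origin of 25: 21 × 1.2 = 25.2, rounded down. The article does not show the step, so this is an inference.
- As randomised, assuming an even split of 52: 26 × 0.80 = 20.8, still below 21.

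**Step 3: operating characteristics at the evaluable number reached.**

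| Evaluable n | Cut-off | Type I error | Power |
|---|---|---|---|
| 21 | 8 | 0.043 | 0.905 |
| 20 | 8 | 0.032 | 0.868 |
| 20 | 7 | 0.087 | 0.942 |

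With 20 evaluable patients, no cut-off meets both limits. Keeping the type I error below 0.05 requires 8 responders, and the miss rate is 1 − 0.868 = 13.2%.

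**Step 4: the loss that each target can absorb and still leave 21 evaluable.**
- 25 per arm: 4 losses, 4/25 = 16%.
- 26 per arm: 5 losses, 5/26 = 19.2%.

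**Step 5: allowing for chance in the number lost.** If each patient is lost independently with probability 0.20, the probability of at least 21 evaluable is 0.42 with 25 randomised, 0.58 with 26 and 0.71 with 27.

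**The case against.** The arithmetic slip is hard to contest; its weight can be.

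- **Withdrawal is not the same as loss of the biopsy.** A patient counts as evaluable whatever amount of treatment was received, so someone who stops treatment may still be biopsied. This is true, and the figure of 20 assumes that every withdrawal loses the biopsy. But the sample size section uses the withdrawal rate in exactly that way, to protect the evaluable count.
- **20% is the top of the cited range.** At 10% loss, 25 × 0.90 = 22.5 remain, and the shortfall appears only above 16%. This also stands, but the article says that it planned for 20%.
- **52 were randomised.** Under an even split the expected shortfall is 0.2 of a patient per arm, and 21 is more likely than not to be reached. The problem shrinks but does not disappear. The two extra patients were admitted because they had already consented and were eligible, not to correct the inflation. The decision rule concerns the liraglutide arm only, so the test itself does not need 27 on placebo.
- **Power does not rise steadily with n.** If the cut-off is re-derived to hold the type I error at 0.05, 22 evaluable patients need 9 responders and power is 0.857; 23 also need 9, with power 0.895; 24 need 9, with power 0.924. Averaged over independent 20% losses, power is 0.850, 0.864 and 0.878 for 25, 26 and 27 randomised. So the 16% figure describes reaching 21 patients. It does not guarantee 0.90 power at every smaller loss, and 27 per arm would not guarantee it either. This limits how the correction should be worded; it does not rescue the article's statement.

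**Conclusion.** The concern holds. Twenty-five per arm does not account for 20% withdrawal when 21 evaluable patients are required. At the plan's own rate, 20 remain and power is 0.868 instead of the 0.905 of the 21-patient design. The type I error falls to 0.032, so there is no added risk of a false positive.

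The shortfall is small: one evaluable patient, or two randomised patients, per arm. It rests on p0 = 0.20 and p1 = 0.50 as stated, on withdrawal meaning no final biopsy, and on the cut-off of 8 being kept at n = 20. The figure of 20.8 for the trial as recruited further assumes an even split of the 52. The base design of 21 with cut-off 8 is not in question.

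**What to change.** Recruitment is closed, so correct the statements in Sample size justification and in the abstract:

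1. Remove the claim that 25 per arm preserves 0.90 power after 20% withdrawal, and note that 21 / 0.80 gives 27 per arm.
2. State that 25 per arm yields 21 evaluable patients if no more than 16% are lost, and 26 per arm if no more than 19% are lost. Word this as reaching 21 patients, not as assured power over that range.
3. State that at 20% loss about 20 patients per arm are evaluable, with cut-off 8, one-sided type I error 0.032 and power 0.87.
4. When results are reported, give the type I error and power at the evaluable number actually reached on liraglutide.

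The cost is a change of text and a slightly less favourable power figure. The 8-of-21 rule, the data collected and the conduct of the trial are unaffected.

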### Analysis of outcome measures

All evaluable patients will be analysed on the intention-to-treat principle. Evaluable patients are defined as those who have had an end-of-treatment biopsy (visit 7), irrespective of the amount of treatment they have received. Patients will be categorised as either achieving the primary histological endpoint (ie, disappearance in NASH) or not. The proportion of patients with a reported improvement in liver histology will be presented and compared across treatments descriptively with 95% CIs. The proposed A'Hern's design stipulates that 8 or more evaluable patients of 21 in the experimental treatment group (liraglutide) need to achieve the defined improvement in liver histology for treatment with liraglutide to be deemed worthy of further investigation with a phase III trial. Analyses will be presented for the subgroups of patients with and without T2D. Patients who have not had an end-of-treatment biopsy will be classed as non-evaluable and will not be included in the primary analysis.

Secondary analysis of the primary outcome measure will report (1) the number and proportion of patients that did not have an end-of-treatment biopsy and the reasons for this (these will be classified as ‘no histological improvement’) and (2) the number and proportion of patients that were considered to have had sufficient treatment and an end-of-treatment biopsy. In addition, an analysis that directly compares the two proportions for the separate treatment arms will be performed using the χ^2^ test.

Secondary measures collected as continuous and categorical variables will be presented with 95% CIs descriptively across treatments using medians and proportions, respectively. Secondary measures collected as longitudinal data (including QOL data, scored as per the questionnaire-specific scoring manuals) will be presented descriptively across treatment groups as changes over time. A summary of all adverse events (AEs) experienced by patients in both arms will be reported.

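### The primary analysis is labelled intention-to-treat but is an evaluable (complete-case) analysis, and its only go cut-off, 8 of 21, does not carry over to a larger denominator

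*Protocol article*

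**What the plan says.** The label appears three times. The abstract (Methods and analysis) announces an "intention-to-treat analysis of the proportion of evaluable patients achieving an improvement in liver histology", and Study design overview repeats this in nearly the same terms. Analysis of outcome measures says: "All evaluable patients will be analysed on the intention-to-treat principle".

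That section then defines evaluable as having had the visit 7 biopsy, however much treatment was taken, and adds: "Patients who have not had an end-of-treatment biopsy will be classed as non-evaluable and will not be included in the primary analysis".

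The go rule in the same section is 8 or more responders among 21 evaluable liraglutide patients. No cut-off is given for any other number.

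A secondary analysis of the primary outcome reports the patients without a biopsy, with reasons, and classes them as having no histological improvement. A chi-squared comparison of the arms is also planned, and the article does not say on which set.

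Sample size justification cites withdrawal of 10–20% in earlier NASH trials and plans for 20%, with 25 patients per arm. Trial status reports that 52 were randomised.

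**The concern.** Intention-to-treat has two parts: patients are analysed in the arm to which they were randomised whatever treatment they took, and all randomised patients are included. The plan keeps the first part and drops the second. Attending for a second liver biopsy at week 48 happens after randomisation and may depend on tolerability or perceived benefit. The article gives reasons to expect some loss: its own 20% allowance and, under Challenges in trial design, patients' reluctance to be biopsied again. It gives no rates by arm.

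Two things are at stake. A reader who takes the label at face value will think that the headline proportions and intervals cover everyone randomised. And the false-go rate of the decision rule may not be the stated 5%, either because the evaluable set is enriched for responders or because the count of 8 is applied to a denominator for which it was not derived.

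**Working it through.** **Inputs.** From Sample size justification: the method ("The sample size was calculated using A'Hern's single stage phase II methodology"), significance level 0.05, power 0.90, the null rate ("It was estimated that 20% of the placebo-control arm would achieve an improvement in liver histology", so p0 = 0.20), the target ("a clinically relevant improvement in liver histology was required in at least 50% of patients", so p1 = 0.50) and the size ("The design required 21 evaluable patients in the treatment group"). From Analysis of outcome measures: go if at least 8 respond. From Trial status and Randomisation: 52 randomised 1:1. The split by arm is not given, so 26 per arm is an assumption.

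**Formula.** P(X ≥ r | n, p) = Σ C(n,k) p^k (1−p)^(n−k), summed over k = r to n. The test is one-sided, as is usual for this design; the article does not state the side.

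**1. The plan's own design.** P(X ≥ 8 | 21, 0.20) = 0.0431 and P(X ≥ 8 | 21, 0.50) = 0.9054. A search over n confirms 21 as the smallest number that meets both requirements. The stated design is reproduced.

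**2. Effect of dropping patients without a biopsy.** Removing patients leaves the number of observed responders unchanged and reduces the denominator, so the evaluable rate is equal to or higher than the rate with no biopsy counted as no improvement. To size the worst case, let the true all-randomised rate be 0.20, let every patient without a biopsy be a failure, and let a fraction d be missing. The rate among evaluable patients is then 0.20/(1−d).

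| Missing d | Evaluable rate | P(X ≥ 8 of 21) |
|---|---|---|
| 0 | 0.200 | 0.043 |
| 10% | 0.20/0.90 = 0.222 | 0.074 |
| 20% | 0.20/0.80 = 0.250 | 0.130 |

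If missingness is unrelated to response, the evaluable rate stays at 0.20 and the first row applies whatever d is.

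**3. The cut-off for other denominators.** Null rate 0.20 throughout. The last two columns give the smallest r with tail probability at most 0.05, and that probability.

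| n counted | P(X ≥ 8) | Smallest r | P(X ≥ r) |
|---|---|---|---|
| 21 | 0.043 | 8 | 0.043 |
| 22 | 0.056 | 9 | 0.020 |
| 23 | 0.072 | 9 | 0.027 |
| 24 | 0.089 | 9 | 0.036 |
| 25 | 0.109 | 9 | 0.047 |
| 26 | 0.131 | 10 | 0.023 |

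At 26, a cut-off of 9 would give 0.059, so 10 is needed. With 26 in the liraglutide arm, 22 or more are evaluable whenever 4 or fewer lack a biopsy, that is, 15% or less (4/26 = 0.154). This is inside the 10–20% range that the article cites.

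**4. Power of an all-randomised check.** If 20% lack a biopsy and half of the rest respond, the all-randomised rate is 0.80 × 0.50 = 0.40 and P(X ≥ 10 | 26, 0.40) = 0.636. With 10% missing it is 0.90 × 0.50 = 0.45 and P(X ≥ 10 | 26, 0.45) = 0.806.

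**The case against.** A reader might infer that withdrawals can by themselves turn a no-go into a go. The documents do not support that. The only written rule is a count of 8, and dropping patients never adds a responder. Eight of 21 is a go, and 8 of 25 or 26 is not, only if the cut-off is re-derived for the larger denominator against a 20% null.

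Even that reversal rests on taking 20% as a rate per randomised patient. The article draws on earlier trials without saying whether their rates were per randomised or per biopsied patient. If 20% is per biopsied patient and 20% lack a biopsy, the matching all-randomised null is 0.80 × 0.20 = 0.16. Then P(X ≥ 8 | 25, 0.16) = 0.036 and P(X ≥ 8 | 26, 0.16) = 0.045, both still below 0.05.

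It is equally tempting to say that the evaluable rate will be biased upwards. That needs the missing patients to be mainly non-responders, and nothing in the article says so.

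It can also be said that the exclusion is stated openly, that the word evaluable stands beside the label, that the missing patients are reported and classed as not improved in a secondary analysis, and that the primary aim is expressly not a comparison with placebo. All of this stands. Randomisation therefore matters less for the single-arm decision than for the comparison of arms. The set for the chi-squared test, taken alone, could be left to an analysis plan.

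Finally, the trial was sized on 21 evaluable patients. Moving the decision itself to all randomised patients would cut power from 0.905 to about 0.64 at the planned loss. That is a fair reason not to move it.

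None of this makes the label correct or supplies a cut-off for 22 or more patients.

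**Conclusion.** The point holds in a limited form. The analysis called intention-to-treat in the abstract, Study design overview and Analysis of outcome measures is a complete-case analysis of patients with a week-48 biopsy. That is an error in what the article states, independent of any assumption.

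The effect on the false-go rate is conditional. It ranges from none, if biopsies are missing at random, to 0.074 or 0.130 instead of 0.043 at 10% or 20% missing, if every missing patient is a failure and the true all-randomised rate is 20%.

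The gap in the go rule does not depend on why biopsies are missing. Applied as a fixed count to more than 21 patients, 8 responders gives a type I error of 0.056 at 22, rising to 0.109 at 25 and 0.131 at 26 (26 per arm being assumed).

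**What to change.** 1. Remove the intention-to-treat label from this analysis in all three places and call the set the evaluable (complete-case) population.
2. Report the all-randomised analysis, with no biopsy counted as no improvement, with equal prominence for proportions and 95% CIs, and use it for the chi-squared comparison of the arms.
3. Keep the A'Hern decision on the evaluable set for which it was sized, and state before unblinding the cut-off for the number reached: 8 of 21, 9 of 22 to 25, 10 of 26.
4. Show the all-randomised liraglutide result against its own cut-off (9 of 25, or 10 of 26) as a prespecified robustness check. Say that it does not override the decision, and whether the 20% null is meant per randomised or per biopsied patient.

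The cost is wording and a fuller report of a classification already in the plan; no new data are needed, and follow-up was still under way when the article appeared. The drawback is that the all-randomised rate will be equal or lower, and the check at 10 of 26 has only about 64% power if 20% lack a biopsy and half of the rest respond (about 81% if 10% lack one). A failed check would therefore be weak evidence against the drug.
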